### Study Objectives and End points

The primary objective is to demonstrate noninferiority of the ultrashort course of the 1H_3_P_3_ TPT regimen compared with the standard 3HR regimen in preventing active TB, as measured by the 24-month cumulative incidence of active TB following randomization. The secondary objectives include: (1) to compare safety, patient-reported quality of life, and treatment discontinuation rates attributable to AEs between the regimens; (2) to evaluate treatment adherence using protocol-defined completion criteria; (3) to assess acquired *M tuberculosis* drug resistance among participants who develop active TB after TPT; and (4) to establish a contemporary nonintervention cohort for exploratory comparison, delineating the natural progression to active TB among individuals with high-risk LTBI in whom active TB has been ruled out.

The primary end point is a composite of bacteriologically confirmed or clinically diagnosed active TB within 24 months after randomization. Bacteriologically confirmed active TB refers to *M tuberculosis* identification via ≥1 sputum culture and/or molecular assay (eg, GeneXpert MTB-RIF) with detectable bacterial load. Clinically diagnosed TB combines objective clinical symptoms (≥2 of the following: cough ≥2 weeks, fever, night sweats, weight loss >10%, or hemoptysis) and imaging findings highly suggestive of active TB (eg, cavity or nodular lesions on chest CT), after exclusion of alternative diagnoses. Secondary end points include severity-graded AEs, treatment discontinuation (defined as any permanent cessation prior to regimen completion), treatment completion (defined as completing ≥90% of scheduled doses within 110% of the planned treatment duration), all-cause mortality, and acquired drug resistance determined by drug susceptibility testing or targeted molecular assays of *M tuberculosis* isolates from active TB cases. Exploratory analysis will use the nonintervention cohort to establish the background incidence of active TB, against which the risk reduction of each TPT regimen can be calculated. Patient-reported outcomes (PROs) will be calculated using health state utility values and EuroQol visual analog scale scores.

### Randomization and Sample Size Calculation

Enrolled LTBI participants linked to the same index case will be defined as a cluster [14,15], with an assumed average cluster size of 4 participants. Cluster-level randomization will be triggered when ≥1 eligible participant is enrolled within a cluster. Randomization sequences will be pregenerated by the study statistician using SAS (version 9.4; SAS Institute Inc) and will not be accessible to any personnel involved in enrollment, assignment, or intervention delivery. Designated personnel will perform centralized randomization via the interactive web response system. Randomization results will be relayed to the respective site investigators. This is an open-label study, and all participants within the same cluster will receive identical group assignments. To address intercenter heterogeneity, a 2-stage randomization strategy will be applied: in the first stage, stratification by study site will balance baseline characteristics across centers; in the second stage, permuted block randomization (block size=4) within each site will ensure immediate group balance during participant enrollment.

On the basis of surveillance data from China’s National Tuberculosis Control Program, we estimate that the 2-year cumulative active TB incidence among LTBI participants will be 7% [16,17]. Both the 3HR and 1H_3_P_3_ regimens are assumed to have 70% protective efficacy (ie, reducing the 2-year cumulative incidence of active TB into 2.1%).

The intracluster correlation coefficient (ICC) was incorporated into calculations. A systematic review reported ICC values of 0.028 (range 0.0005‐0.21) for school-based clusters [15], while the National Institutes of Health Pragmatic Trials Collaboratory suggested a range of 0.01 to 0.05 [18]. Therefore, we adopted a conservative ICC estimate of 0.05 for this study.

Using these parameters and a prespecified noninferiority margin of a 20% relative reduction in protective efficacy, a total of 396 clusters (n=1584 participants) per treatment arm are required to achieve 80% power at a 1-sided *α*=.05. This sample size is calculated to satisfy the clinically meaningful noninferiority margin, accounting for the cluster randomized design (ICC=0.05, average cluster size=4). Accounting for a 10% attrition rate to mitigate the impact of loss to follow-up on statistical power and outcome validity, each arm will enroll 1760 participants.

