#### Enrollment of LTBI Contacts

Contacts testing positive on QuantiFERON-TB Gold Plus (QIAGEN N V) will subsequently receive chest computed tomography (CT) or chest X-ray, as well as pooled sputum nucleic acid amplification testing (eg, GeneXpert MTB-RIF [Danaher Corp]) to exclude active TB. LTBI is defined as a positive interferon-gamma release assay result without evidence of active TB. Those with confirmed LTBI and aged ≥13 years are eligible for this trial. Study protocols will be thoroughly explained to eligible participants by site investigators, with written informed consent obtained prior to enrollment. Parental or guardian consent is mandatory for minors (aged <18 years). Participants meeting the inclusion criteria but declining enrollment in the TPT trial will be invited to join a supplemental nonintervention cohort. After providing separate informed consent, they will be followed for 24 months to monitor for the development of active TB. Further eligibility validations will require review of medical history and comprehensive laboratory evaluations to exclude contraindications to TPT. Textbox 1 shows the detailed inclusion and exclusion criteria.

Textbox 1.Inclusion and exclusion criteria for the TB-YOUTH study.

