### Statistical Analysis

Statistical analyses will be performed using SAS and R (R Foundation for Statistical Computing). Multiple imputation will be conducted to handle missing data, with additional inverse probability weighting applied for the nonintervention cohort to adjust for potential attrition bias. Continuous variables will be summarized as mean (SD) or median (IQR), as appropriate. Categorical variables will be summarized as counts and percentages.

The primary analysis will assess the noninferiority of the 1H_3_P_3_ regimen compared to the 3HR regimen in preventing active TB over the 24-month follow-up period, and the primary end point is the composite of bacteriologically confirmed or clinically diagnosed active TB. To account for the cluster randomized design and the inherent correlation within clusters, we will use a Cox proportional hazards regression model with shared frailty terms and exact likelihood estimation. Noninferiority of the 1H_3_P_3_ regimen relative to the 3HR regimen will be concluded if the analysis demonstrates that the 1H_3_P_3_ regimen does not experience a ≥20% relative reduction in protective efficacy for preventing active TB over the 24-month follow-up period. To enhance precision and address potential baseline imbalances despite randomization, the model will adjust for key prespecified covariates, such as age, sex, BMI, characteristics of the index case (smear or cavitation status), and cluster size. Outcomes will be assessed via 2 prespecified analyses with explicit definitions: the modified intention-to-treat population includes all randomized participants who received at least 1 dose of the study medication, analyzed by the assigned treatment group regardless of subsequent protocol deviations or treatment discontinuation; the per-protocol population includes all randomized participants who completed ≥90% of scheduled doses within 110% of the planned treatment duration without major protocol deviations (including use of prohibited concomitant anti-TB medications, enrollment despite exclusion criteria, or unblinding to outcome assessors). Prespecified subgroup analyses will examine treatment effect heterogeneity by age (13-17 years vs ≥18 years) and index case features (smear or cavitation status), tested through interaction terms in Cox models (interaction *P*<.10).

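### Read literally, the randomisation trigger lets cluster members enrol knowing their arm, and no section requires the roster to be closed first

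*Protocol article*

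**What the plan says.** In the protocol article, Randomization and Sample Size Calculation gives the trigger: "Cluster-level randomization will be triggered when ≥1 eligible participant is enrolled within a cluster". The same section adds: "This is an open-label study, and all participants within the same cluster will receive identical group assignments". On who learns the arm: "Randomization results will be relayed to the respective site investigators". Concealment is promised for the pregenerated sequence, which "will not be accessible to any personnel involved in enrollment, assignment, or intervention delivery". The allocation method is "permuted block randomization (block size=4) within each site".

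Enrollment of LTBI Contacts gives consent to the same people: "Study protocols will be thoroughly explained to eligible participants by site investigators, with written informed consent obtained prior to enrollment". On decliners it says: "Participants meeting the inclusion criteria but declining enrollment in the TPT trial will be invited to join a supplemental nonintervention cohort". The exclusion criteria (Textbox 1) end with an item left to the investigator's judgement.

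Under Statistical Analysis, the modified intention-to-treat set "includes all randomized participants who received at least 1 dose of the study medication". The per-protocol set requires at least 90% of doses within 110% of the planned duration.

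**The concern.** In a cluster-randomised trial, randomisation protects the comparison only for people whose entry was settled before the arm was known. If a cluster is allocated on its first enrolment, the remaining contacts may be approached by investigators who know whether they are offering 12 doses over one month or 90 daily doses over three.

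The protocol itself makes differential uptake plausible. The Introduction attributes low adherence and completion on 3HR in China to its length and toxicity. If uptake differs by arm, the arms may differ in size, in health-seeking and in underlying TB risk. In a noninferiority comparison, a bias in either direction can help decide the verdict.

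**Working it through.** **1. Is arm-aware entry allowed?**

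- The trigger sentence allows allocation at the first enrolment.
- The result goes to the site investigators, who also explain the study and take consent.
- Concealment covers the future sequence, not the known arm of a cluster already randomised.
- Study Design has eligible contacts grouped into clusters and the clusters then randomised. TPT Intervention likewise speaks of clustered eligible participants undergoing randomisation. Table 2 puts eligibility and consent in the –30 day column and allocation at day 0.
- No section says that all members must have consented before allocation, or that later members are recruited by someone unaware of the arm.
- The Discussion assigns clusters by the earliest identified index case when there are several possible sources. A contact found through a later case could therefore fall into a cluster already allocated.

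The text permits late entry without saying that it happens.

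**2. How many could be affected?**

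The plan's figures are 396 clusters × 4 = 1584 per arm, and 1584 / 0.90 = 1760. With a trigger at the first of 4, at most 3/4 = 75% enter after allocation (1188 of 1584 per arm). Enrolment to the end of December 2025 was 2478 participants and 627 index cases, or 3.95 per index case. Taking one cluster per index case, the upper bound is 2478 − 627 = 1851, or 74.7%.

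**3. Can the analysis sets undo it?**

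Both start from randomised participants, so a contact who refuses knowing the arm is in neither. The one-dose and 90%-of-doses conditions are also met or missed after the arm is known. The named covariates (age, sex, BMI, index-case features, cluster size) adjust only for what is measured, and cluster size may itself depend on the arm if uptake differs.

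**4. Illustrative size**

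Assumptions, none of them from the documents: a share q = 0.20 of late-approached contacts refuse only when offered 3HR; nobody refuses only 1H3P3; refusers have r times the TB risk of the others; first members are a typical mix. Let s be the late share.

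- Mean relative risk, 1H3P3: M = (1 − q) + q·r
- Mean relative risk, 3HR: [(1 − s)·M + s·(1 − q)] / (1 − s·q)
- Bias factor on the hazard ratio, treated as a risk ratio at low incidence: F = M divided by the 3HR mean

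Margin as worded: efficacy 70% × 0.80 = 56%; incidence 7% × 0.44 = 3.08%; ln(3.08/2.1) = 0.383.

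| Late share | r | Calculation | F | Share of log margin |
|---|---|---|---|---|
| 75% | 0.5 | 0.9 / [(0.25×0.9 + 0.60)/0.85] | 0.927 | 20% |
| 75% | 2 | 1.2 / [(0.25×1.2 + 0.60)/0.85] | 1.133 | 33% |
| 25% | 0.5 | 0.9 / [(0.75×0.9 + 0.20)/0.95] | 0.977 | 6% |
| 25% | 2 | 1.2 / [(0.75×1.2 + 0.20)/0.95] | 1.036 | 9% |

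A factor below 1 favours noninferiority; above 1 works against 1H3P3. The 3HR clusters shrink by 15% at 75% late entry and by 5% at 25%.

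**5. Predictability of the next allocation**

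A 1:1 block of 4 has 6 orders and so 24 positions. The fourth position is always fixed by the first three (6 positions). The third is fixed when the first two match (2 positions). Thus 8/24 = 33% of cluster allocations can be deduced by a site that tracks its block boundaries.

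**The case against.** The strongest reply is that the trigger only sets a minimum cluster size, so that a cluster of one qualifies. Study Design, TPT Intervention and Table 2 all put grouping or consent before allocation, and a cluster is defined by its enrolled participants. Contacts of an index case are also screened in one cascade. The exact order of consent and web-system call could be left to the full protocol.

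Much of this stands. A reader might infer that everyone after the first contact is in fact approached with the arm known. The documents do not say so. Nor do they say that anyone declines after learning the arm: the sentence on decliners does not mention allocation and comes before the further eligibility checks. The 75% is a ceiling.

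What does not stand is that the question is therefore settled. The article states the trigger rule itself, and that rule allows early allocation. None of the sections pointing the other way requires a complete roster.

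Two further cautions are fair. The block-size point is a separate weakness that mainly concerns first consenters, and it depends on sites tracking blocks. The effect of the one-dose condition cannot be sized, because the article gives no number for participants who are randomised but never dosed.

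**Conclusion.** The point holds as an unreconciled rule that leaves arm-aware enrolment open, not as proof that it has occurred. It should be fixed.

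Under the stated assumptions, the shift ranges from 6% to 33% of the log margin as the late share goes from 25% to 75%. A reader might infer a bias as large as the margin; even the maximum late share does not give that here. The actual late share, the refusal rate and the refusers' risk are all unknown, and so is the direction of any bias.

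**What to change.** **Clusters still to come**

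- State in the randomisation section that consent and eligibility are completed for all IGRA-positive contacts in the screening round before the web system is called. Bring Study Design, TPT Intervention, Table 2 and the trigger sentence into line.
- Leave people who join after allocation out of the primary analysis.
- Analyse all other randomised participants as assigned, and keep the one-dose set as a sensitivity analysis.
- Use randomly varying, undisclosed block sizes for the remaining allocations.

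**Clusters already randomised**

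- Compare consent and allocation dates where these were recorded. The article does not confirm that both are available.
- Report uptake and refusals by arm.
- Repeat the primary analysis without people who consented after allocation.

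**Cost and reach.** This takes a short amendment and a change to the web-system settings. The target stays at 1760 per arm, and the first consenter may wait briefly while the roster closes. By the end of December 2025, 2478 of 2 × 1760 = 3520 participants had been enrolled, leaving 1042, or about 30%, whom roster closure could still protect. For the rest, only the reporting and the sensitivity analysis are available.

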## Methods

### Study Design

This is a multicenter, prospective, cluster randomized, noninferiority clinical trial comparing the protective efficacy and safety of the 1H_3_P_3_ regimen with those of the 3HR regimen for TPT in adolescents and adults with LTBI. Prior to trial initiation, close contacts of pulmonary TB index cases within school environments will undergo active screening through the TB-YOUTH Screening program, a cross-sectional study (ClinicalTrials.gov NCT06033807), under the auspices of the National Tuberculosis Control Program in China. After excluding active TB, eligible LTBI participants will be grouped into clusters by their corresponding index cases. The clusters will then be randomized in a 1:1 ratio to receive either the 1H_3_P_3_ or the 3HR regimen for TPT. Medication adherence and adverse events (AEs) will be monitored at week 2, month 1, and month 2 for the 1H_3_P_3_ group, and at week 2 and then monthly until month 4 for the 3HR group after treatment initiation. Participants will undergo follow-up clinical assessments every 6 months for 2 years following randomization. The preventive efficacy of each study arm against active TB will be evaluated at the conclusion of the follow-up period.

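### A single block size of 4 within site, published while an open-label trial is still recruiting, could let staff who track allocations deduce up to one cluster allocation in three

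*Protocol article*

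**What the plan says.** The unit and ratio are given under Study Design: "The clusters will then be randomized in a 1:1 ratio to receive either the 1H_3_P_3_ or the 3HR regimen for TPT". The rest is in Randomization and Sample Size Calculation.

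- Site is the only stratification factor named: "stratification by study site will balance baseline characteristics across centers". Within site, "permuted block randomization (block size=4) within each site will ensure immediate group balance during participant enrollment".
- The trial is unblinded: "This is an open-label study, and all participants within the same cluster will receive identical group assignments".
- Sites learn each outcome: "Randomization results will be relayed to the respective site investigators".
- Two safeguards are stated. The sequences "will not be accessible to any personnel involved in enrollment, assignment, or intervention delivery", and "Designated personnel will perform centralized randomization via the interactive web response system".
- The trigger is early: "Cluster-level randomization will be triggered when ≥1 eligible participant is enrolled within a cluster".

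Nothing in the article says that block sizes vary or are withheld from sites. The Results section puts enrolment at 2478 participants and 627 index cases by the end of December 2025, with recruitment continuing to about September 2026.

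**The concern.** Concealment has two parts: staff must not be able to read the list, and they must not be able to work out the next entry from what they have already seen. The stated safeguards deal with the first part only. With open treatment, one block size, one sequence per site and every result returned to the site, the second part depends on staff not knowing the block size or not keeping count.

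Foreknowledge matters only where staff can act on it, and they have some room to do so. Under Enrollment of LTBI Contacts, site investigators explain the study and obtain consent, and eligible people who decline are offered a nonintervention cohort. The exclusion criteria in Textbox 1 end with an item left to investigator judgement. Table 2 places enrollment procedures up to 30 days before allocation. The arms are also easy to prefer between: 12 doses against 90 (TPT Intervention), and the Introduction attributes poor 3HR adherence in China to duration and toxicity.

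At stake is the comparability of the arms in an analysis with few events. At the planned 2.1% incidence and 1584 participants per arm, about 0.021 × 1584 = 33 events per arm are expected, so modest selection on baseline risk could move the noninferiority estimate.

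**Working it through.** The article gives no predictability figure to reproduce, so this is a direct enumeration.

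**Inputs.** Block size 4, ratio 1:1, blocks within site, past allocations known (Randomization and Sample Size Calculation; Study Design). I take the block to count clusters, since clusters are what is randomized.

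**Certain knowledge, complete blocks.** The six equally likely blocks are AABB, BBAA, ABAB, ABBA, BABA and BAAB. An allocation is certain once one arm has used its two places.

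- In AABB and BBAA, positions 3 and 4 are certain: 2 per block.
- In the other four, only position 4 is certain: 1 per block.
- Expected number per block = (2×2 + 4×1)/6 = 4/3, so the share is (4/3)/4 = 1/3.
- By position: 0%, 0%, 33.3%, 100%.

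**Best guess.** Guess the arm with more places left; at a tie the chance is 1/2. The success rates by position are 1/2, 2/3, 2/3 and 1. Their mean is (17/6)/4 = 17/24 = 70.8%.

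**Incomplete blocks.** The expected share certain for a site with n clusters is the sum of the position probabilities divided by n:

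- n = 1 or 2: 0%
- n = 3: (1/3)/3 = 11%
- n = 5: (4/3)/5 = 27%
- n = 30: (7 × 4/3)/30 = 31%

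The article does not give the number of sites, so the trial-wide share lies somewhere at or below one third.

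**Alternatives.** For a fixed block of size 2m the certain share is 1/(m+1). For randomly varied sizes, a simulation of 20,000 allocations used an observer who knows the set of sizes but not where blocks begin and end.

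| Scheme | Certain | Best guess right |
|---|---|---|
| Fixed 4 | 33.3% | 70.8% |
| Fixed 6 | 25% | 68.3% |
| Fixed 8 | 20% | 66.6% |
| Random 4, 6 | about 5.7% | about 69% |
| Random 4, 6, 8 | about 2.1% | about 68% |

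Varied sizes remove nearly all certainty but little of the guessing advantage.

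**Scale.** The target is 2 × 1760 = 3520 participants; at 4 per cluster, 880 clusters. Less the 627 index cases enrolled, 253 remain. Counting by participants, (3520 − 2478)/(2478/627) = 1042/3.95 ≈ 264. Both support about 250 as of December 2025. Of the 627 already randomized, at most about 627/3 = 209 would be expected in predictable positions.

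**The case against.** The strongest reply is that one in three is a ceiling. It needs staff who know the block size, have followed every allocation at their site and work in complete blocks. The article does not say that sites were told the block size, and the sequences were withheld from enrolling staff. This stands, and the point is worded accordingly. A reader might infer that sites have known the block size throughout. The document does not support that: the only disclosure shown is the article itself, and the full protocol is not available.

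Second, control over clusters is limited. A cluster begins with a surveillance notification verified by the local Centers for Disease Control and Prevention; contacts are defined by guideline, and infection status rests on testing. Reordering clusters would need several pending at one site at once, which is not shown. This also largely stands. What remains is discretion over timing, the consent discussion and the judgement-based exclusion. Eligible decliners are invited to a followed cohort, which would make selective non-enrolment partly visible.

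Third, the primary model in Statistical Analysis adjusts for age, sex, BMI, index-case smear or cavitation status, and cluster size. These are plausible selection variables, so the adjustment helps, but only for measured factors.

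A reader might also infer that the arms already differ in baseline risk. The calculation measures predictability, not bias, and the document offers no evidence that anyone has used such knowledge.

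Finally, small blocks give good balance within site. That is a real benefit, but it does not require the block size to be constant or published.

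**Conclusion.** The point holds as a design weakness that is cheap to reduce. The article contains no error or contradiction here. Staff who know the block size and track their site's allocations could foresee up to 33% of allocations with certainty, on average over complete blocks, and guess up to 71% correctly. Concealing the list and randomizing centrally do not change that. Selective enrolment is possible rather than demonstrated, and the planned adjustment would address part of it.

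This assumes that blocks count clusters, that each contains two of each arm, and that a site's past allocations are known to those who enrol there. The share that applies in practice depends on the number of clusters per site, which the article does not give, and on whether staff knew or inferred the block size.

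**What to change.** For clusters not yet randomized, load a new list into the web response system with block sizes varying at random (for example 4, 6 and 8), and disclose neither the sizes nor their order to sites. Start it at the next cluster at each site, whether or not the open block of 4 is complete; otherwise the remaining places in that block stay deducible. The gain is the fall in certain knowledge from 33% to about 2%; the best-guess rate should not be expected to approach 50%.

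The new list cannot reach clusters already randomized. For those, prespecify a comparison of baseline risk by arm (index-case smear or cavitation status, age, cluster size) restricted to predictable allocations: every fourth position, and third positions where the first two went to the same arm. The statistician holding the list can identify these.

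The cost is one new list, a system update and slightly looser balance. Within a block the arms at a site could differ by up to 4 clusters with a block of 8, against 2 with a block of 4, plus up to 2 carried over from an abandoned block. This matters mainly at small sites. The number of clusters that can benefit shrinks as recruitment proceeds, so the change is worth making soon.

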**Methods:**

An investigator-initiated, prospective, multicenter, open-label, noninferiority, cluster-randomized controlled clinical trial is being implemented under the auspices of the national TB control program in China. Close contacts of school pulmonary TB index cases, regardless of diagnostic type, are actively screened for symptoms using interferon-gamma release assays, chest imaging, and sputum molecular diagnostic testing to detect TB infection and exclude active TB. Eligible latent TB infection cases will be randomized in a 1:1 cluster ratio to receive either the standard 3HR regimen or the novel ultrashort 1H_3_P_3_ regimen for TPT, with subsequent follow-up for up to 2 years to assess disease progression. The primary composite end point includes microbiologically confirmed TB (sputum culture or molecular diagnostic testing) or clinically diagnosed TB. With 80% power to detect noninferiority (20% margin), the study requires 1760 participants per arm, accounting for cluster design effects.

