China has prioritized school TB control, with provincial Centers for Disease Control and Prevention in high-burden areas implementing expanded screening programs to detect TB cases among students [29]. Despite operational challenges, this study aligns with national efforts and receives multisectoral support from education authorities and social media platforms. As evidenced by the “zero TB” initiative in India, community-engaged strategies can achieve excellent TPT acceptance and adherence [10].

Cluster randomization was adopted for several reasons. First, participants in close-contact settings (eg, classmates and dormitory residents) have prolonged shared exposure, increasing the risk of intracluster interference. Second, distinct intervention protocols between groups (daily vs intermittent dosing) could cause confusion if implemented individually. Cluster-level administration allows mutual adherence reminders among participants, potentially enhancing adherence. Teachers and other school staff meeting close-contact criteria will be coenrolled in the same cluster as students to maintain intervention homogeneity.

We adopted a 20% relative reduction in protective efficacy as the noninferiority criterion, which is clinically justified and aligns with the core objective of evaluating whether the ultrashort 1H_3_P_3_ regimen retains adequate protective efficacy compared to the standard 3HR regimen. Historical data support this threshold: the 3HR regimen reduces TB incidence from 7% to 2.1% (70% protective efficacy), and a 20% relative reduction in protective efficacy is clinically acceptable for the 1H_3_P_3_ regimen. Although noninferiority is the primary focus, the regimen’s ultrashort duration and favorable safety profile could offer substantial practical benefits for individuals with LTBI.

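### The sample size of 396 clusters (1584 participants) per arm does not give 80% power at the stated margin of a 20% relative loss of efficacy; it matches a 20 percentage-point loss, and power at the stated margin is about 54%

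*Protocol article*

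**What the plan says.** All inputs stand in the Randomization and Sample Size Calculation section of the protocol article:

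- 2-year incidence of 7% without treatment
- 70% efficacy, hence 2.1% incidence, in both arms
- ICC 0.05 and mean cluster size 4
- one-sided alpha 0.05 and 80% power
- 10% attrition

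The margin and the result come in one sentence: "a prespecified noninferiority margin of a 20% relative reduction in protective efficacy, a total of 396 clusters (n=1584 participants) per treatment arm are required". After attrition this becomes 1760 per arm. The Abstract repeats the claim with a less specific margin: "With 80% power to detect noninferiority (20% margin), the study requires 1760 participants per arm, accounting for cluster design effects".

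The margin is relative in two further places. Under Statistical Analysis, noninferiority is concluded if the new regimen "does not experience a ≥20% relative reduction in protective efficacy for preventing active TB over the 24-month follow-up period". The Discussion justifies the margin by saying that "the 3HR regimen reduces TB incidence from 7% to 2.1% (70% protective efficacy), and a 20% relative reduction in protective efficacy is clinically acceptable".

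**The concern.** A 20% relative loss and a 20 percentage-point loss are different limits when efficacy starts at 70%: the relative loss leaves 56%, the percentage-point loss 50%. The text describes a relative loss in the design, the decision rule and the justification, but the sample size fits a percentage-point loss.

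If the trial is judged on the margin it declares, it has about even odds, or worse, of showing noninferiority when the regimens are truly equal. If it is judged on the wider margin, the published criterion is wrong and readers will believe that more efficacy was preserved than was tested. Left open, the choice could fall after the results are known. Any upper confidence bound between the two limits (0.98 and 1.4 points on the risk-difference scale) would then reverse the conclusion.

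**Working it through.** **Two readings of the margin** (7% untreated, 2.1% in each arm)

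| | A: 20% relative loss, as written | B: 20 percentage-point loss |
|---|---|---|
| Lowest acceptable efficacy | 0.70 × 0.80 = 56% | 70 − 20 = 50% |
| Limit incidence | 7% × 0.44 = 3.08% | 7% × 0.50 = 3.5% |
| Absolute margin d | 0.98 points | 1.4 points |
| Risk ratio at the limit | 1.467 | 1.667 |
| Relative loss of efficacy | 20% | 20/70 = 28.6% |

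**Formula.** The Farrington-Manning score test needs, per arm before clustering,

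n = (1.645·√V0 + 0.842·√V1)² / d²

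V1 = 2 × 0.021 × 0.979 = 0.04112 is the variance term with both arms at 2.1%. V0 is the same term at the restricted estimates under the margin: 2.696% and 1.716% for A (V0 = 0.04311); 3.008% and 1.608% for B (V0 = 0.04499). The design effect is 1 + (4 − 1) × 0.05 = 1.15.

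**The plan's own figure (B).** n = 1377.24. Multiplied by 1.15 this is 1583.8, so 1584 participants or 396 clusters of 4. Then 1584/0.9 = 1760. All three printed numbers are recovered, and power at 396 clusters is 80.0%.

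**The margin as written (A).** n = 2731. Multiplied by 1.15 this is 3141 evaluable per arm, and 3141/0.9 = 3490 enrolled. The unpooled (Wald) formula gives 2647 × 1.15 = 3044. Pooled, continuity-corrected, log risk ratio, log odds ratio, arcsine, Schoenfeld and Freedman versions were also tried. At margin A none gives 1584, and none at one-sided alpha 0.05 falls below the Wald figure.

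**Power with 1584 per arm** (effective n = 1584/1.15 = 1377)

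| Test | A: as written | B: 20 points |
|---|---|---|
| Farrington-Manning | 54% | 80% |
| Wald risk difference | 56% | 82% |
| Log hazard ratio | 43% | 63% |

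For the last row, the expected events are 2 × 1377 × 0.021 = 57.9. The hazard-ratio margin is ln(1 − 0.0308)/ln(1 − 0.021) = 1.474 for A. Power is Φ(ln 1.474 × √(57.9/4) − 1.645) = 43%. A beta-binomial simulation (40,000 runs) agrees for A: 56% on the risk difference and 43% on the risk ratio.

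**Sensitivity for A**

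- No clustering effect at all (ICC 0): 59% (Farrington-Manning) or 61% (Wald).
- ICC 0 and all 1760 per arm retained: 63% or 65%.
- Unequal cluster sizes with a coefficient of variation of 1 (an assumption; the article gives no figure): design effect 1 + (4 × 2 − 1) × 0.05 = 1.35, and power about 50% (Wald) or 39% (hazard ratio).

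Reading the 20% instead as a relative rise in incidence (2.1% to 2.52%) does not help: it needs more than 16,000 per arm.

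**The case against.** The strongest reply is that the calculation was sound and only its description slipped. Efficacy is itself a relative risk reduction, so the word relative may be loose wording for 20 points on that scale, and the Abstract says only 20%. The exact match at 20 points supports this. On that reading the trial has its 80% power, and the 54% applies only to a criterion nobody intended.

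This may well be how the error arose, but it does not remove it. The relative wording is in the decision rule itself, and a regimen that lost 20 points of efficacy would fail that rule. Whichever side is wrong, the article needs correcting.

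Three parts of the reply stand:

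- The 20-point margin and the Farrington-Manning method are inferred from the match. The article names neither, and other methods at 20 points give different numbers (Wald 1492, Schoenfeld about 2525).
- The 43% mixes in a second effect, the choice of scale. The article plans a Cox frailty model but states no hazard-ratio margin, and the hazard-ratio scale lowers power at the 20-point margin too.
- Recruitment is planned to September 2026, so enlarging the trial is also open to the sponsor.

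**Conclusion.** The point holds. The stated margin, power and sample size are inconsistent. At the margin as written, 1584 evaluable participants per arm give about 54% power by the same test that reproduces the plan's number, 56% by the Wald test, and about 43% on the hazard-ratio scale. For 80% power about 3141 evaluable per arm would be needed, roughly twice the stated number. These results rest on the article's own inputs: 7%, 70%, ICC 0.05, cluster size 4, one-sided alpha 0.05 and truly equal regimens. The mismatch does not depend on how the authors obtained 1584; only the explanation by a 20-point loss is inference.

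**What to change.** Go back to the original calculation file, establish which margin was agreed, and make margin and power match before any outcome data by arm are seen. There are two routes:

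1. **The relative margin was intended.** Keep it and add its values: efficacy at least 56%, limit incidence 3.08%, 0.98 points. In the Abstract and the sample size section, replace the 80% power by the true figure: about 54%, or about 43% if the hazard ratio is tested.
2. **Twenty percentage points was intended.** In the sample size section, Statistical Analysis and Discussion, replace the relative wording by an absolute loss of 20 percentage points (70% to 50%, limit incidence 3.5%, 1.4 points), and make the Abstract specific. Justify this wider margin afresh, because it gives up 28.6% of the assumed efficacy.

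Under either route, name the scale on which the margin is tested. Under route 2 the 80% holds for the risk-difference score test; on the hazard-ratio scale power is about 63%.

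The cost is a wording amendment and a less favourable power or margin. No extra enrolment is asked for, though the sponsor may choose to re-estimate the sample size while recruitment is open.
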